### Planned endline analysis

For the primary data analysis to determine the effect of the intervention, an intent to treat (ITT) approach will be used, with both community and individual as the unit of analysis. For analyses with individual as the unit of analysis, random effects models and/or generalized estimating equations with robust variance estimators will be used to account for clustering and ensure correct standard errors. All analyses will be weighted and conducted separately for men and women. Multivariate analyses for the primary outcome (endline GEMS score) and secondary outcomes will control for appropriate community characteristics at baseline, such as an aggregate village-level GEMS score.

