### Study design

This study employed a community randomized design to evaluate the impact of the CM intervention in 22 communities (11 intervention) in the study catchment area. To measure the impact of the intervention and monitor changes in study outcomes and the CM domains in each community, two cross-sectional, population-based surveys were implemented among approximately 1,200 randomly sampled adults, ages 18–35 years. The cross-sectional surveys were conducted at baseline in March-June 2012 (prior to intervention implementation) and again in July-September 2014, following approximately two years of intervention implementation. Serial cross-sectional samples were chosen instead of a panel design due to high levels of in- and out- migration in the study population as well as the advantages for measuring community-level indicators and community change in each village.

This study was approved by the Institutional Review Boards at the University of North Carolina-Chapel Hill and University of California-San Francisco, the Human Research Ethics Committee (Medical) at the University of the Witwatersrand in South Africa, and the Mpumalanga Department of Health and Social Development Research Committee.

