### Community randomization

Communities were randomized at a 1:1 ratio, resulting in 11 intervention communities and 11 control communities. In order to achieve a balanced allocation of control and intervention communities with respect to covariates hypothesized to be associated with the primary outcome, gender norms, a restricted randomization scheme was employed [36]. First, all possible two-arm allocations were enumerated and examined to see how they balanced with respect to community characteristics from the 2011 AHDSS that might be associated with gender norms: community population size, average education, number of working residents in the community, number of foreign residents, proportion temporary migrants, and proportion female headed households. A reduced list of 50 allocations from the total 466,918 restricted allocations was randomly chosen and one was selected by a community representative during a community meeting. Community representatives and leaders from all of the communities agreed to participate in the study.

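### With 22 villages, robust GEE or random effects models do not by themselves give correct standard errors, and no route is named as the deciding primary test

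*Protocol article*

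**What the plan says.** The Community randomization section fixes the number of clusters: "Communities were randomized at a 1:1 ratio, resulting in 11 intervention communities and 11 control communities".

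The Planned endline analysis section describes an intention-to-treat primary analysis "with both community and individual as the unit of analysis". For the individual level it says that random effects models and/or "generalized estimating equations with robust variance estimators will be used to account for clustering and ensure correct standard errors". It adds that "All analyses will be weighted and conducted separately for men and women", so each model has 22 clusters with 27 to 28 respondents of one sex per village (Survey sampling). Multivariate models for the primary and secondary outcomes "will control for appropriate community characteristics at baseline, such as an aggregate village-level GEMS score". The number of village-level covariates is not fixed.

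The section names no degrees of freedom, reference distribution or small-sample variance correction, and excludes none. It does not say which unit of analysis or which model governs the primary conclusion.

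**The concern.** The sandwich variance is justified as the number of clusters grows; the number of respondents does not help. With 22 clusters its residuals are too small on average. Each village-level covariate uses up another of the few between-village degrees of freedom and makes this worse. A normal reference then ignores the uncertainty in the variance estimate itself. The same holds, less strongly, for a random-intercept model tested against the normal.

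The sentence therefore credits the named methods with a property that they lack in their ordinary form at this size. What is at stake is the GEMS comparison in each sex: intervals somewhat too narrow, and a nominal 5% test that rejects a true null more often than stated. Because several routes are allowed and their true error rates differ, a result near p = 0.05 could be significant by one route and not by another, with no rule for which counts.

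**Working it through.** **Inputs.** 22 villages, 11 per arm (Community randomization); 27 to 28 respondents per sex per village (Survey sampling); ICC 0.05 (Sample size). That ICC reproduces the plan's design effect: 1 + (55 − 1) × 0.05 = 3.7, and 600 / 3.7 = 162 per arm. The article states no significance level, so two-sided 5% is assumed. Let p be the number of village-level parameters: intercept, arm and any village covariates. Then 22 − p is 20, 19 and 17 with zero, one and three covariates.

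**Closed form, no covariate, balanced villages.** The GEE estimate is the difference in mean village means.
- The uncorrected sandwich divides each arm's sum of squares by 11 instead of 10, so its standard error is √(20/22) = 0.953 of the unbiased one.
- True type I error with a normal reference: P(|t₂₀| > 1.96 × 0.953) = P(|t₂₀| > 1.869) = 7.6%. No ICC value is needed.
- Interval width relative to the correct one: 1.869 / 2.086 = 0.90, about 10% too narrow.

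**Simulation under the null, ICC 0.05.** Two separately coded simulations (6,000 and 10,000 runs per setting) of the uncorrected sandwich with a normal reference:

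| Village covariates | First | Second | Mean SE / true SD (second) |
|---|---|---|---|
| 0 | 7.1% | about 8% | 0.94 |
| 1 | 8.4% | about 8.6% | 0.915 |
| 3 | 11.0% | about 11% | 0.86 |
| 6 | 15.0% | about 16% | 0.76 |

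Standard GEE software with exchangeable correlation (1,500 runs) gave 8.7% with no covariate and 8.6% with one. Varying the ICC from 0.01 to 0.10 changes the no-covariate figure little (7.4 to 8.0%).

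**Random effects models.** For balanced villages and a positive variance estimate, a normal reference gives P(|t| > 1.96) on 22 − p df under REML, and P(|t| > 1.96 × √((22 − p)/22)) under ML.
- REML: 6.4%, 6.5% and 6.7% with zero, one and three covariates (simulated at ICC 0.05: 6.2 to 6.7%).
- ML: 7.6%, 8.4% and 10.3% (simulated: 7.5%, 8.5%, 9.6%).
- At ICC 0.01 the simulated inflation is smaller: 5.4 to 5.7% with REML and 6.4 to 7.0% with ML.

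**Routes that hold the level.**
- Village-level regression with t on 22 − p df: 4.8 to 5.3%.
- REML with t on 22 − p df: 4.6 to 5.3%.
- Kauermann-Carroll sandwich with t on 22 − p df: 5.0 to 6.0%. With no covariate each village has leverage 1/11, so the correction factor 1/(1 − 1/11) = 11/10 = 22/20 restores the variance exactly.
- Mancl-DeRouen sandwich with t on 22 − p df: 4.3% with no covariate, falling to 2.0% with six. The factor is squared, so with no covariate the standard error is √(20/22) × 11/10 = √1.1 = 1.049 of the unbiased one.

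**Sensitivity to what the article does not give.** Unequal village sizes (CV 0.6, assumed) raise the uncorrected figure to 8.7%, 10.0% and 13.2% with zero, one and three covariates. Assumed village weights with CV 0.5 give 8.9%, 10.8% and 13.8%; another assumed weighting, CV 0.6, gives 7.2%, 8.5% and 11.4%. The article does not describe the weights, so none of these is a prediction.

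**The case against.** The strongest reply has three parts.

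First, robust GEE is one permitted route among three. The section also names a community-level analysis and random effects models, which stay near 5% with a t reference. A reader might infer that the primary test rests on GEE alone; the text does not support that. This part stands.

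Second, the words uncorrected and normal reference do not appear. A Kauermann-Carroll sandwich is still a robust variance estimator, and a condensed article may leave corrections and degrees of freedom to a fuller plan. This stands too: the missing detail is not itself the fault. It does not remove the point, because the article goes beyond silence and states that the named methods ensure correct standard errors. That might be read as a loose purpose clause, meaning only that clustering will not be ignored. Even so, someone following the sentence with ordinary software output would get intervals that are too narrow.

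Third, the size depends on the adjustment. A reader might carry away a false-positive rate of 15% or more. That needs six village covariates, or assumed weights in addition (18.1% with both). Six is the number of variables used to restrict the randomization; nothing says that all will enter the model, and the only covariate named is the village GEMS score. Moreover, the simulations allocated villages without restriction. If the balancing variables predict GEMS and are left out of the model, restriction makes the test somewhat more conservative and offsets part of the excess. It kept 466,918 of the 705,432 possible 11:11 splits, about 66%, so it was not tight.

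**Conclusion.** The point holds in a limited form. In ordinary form, two of the permitted routes do not have the property claimed for them at 22 villages. For the sandwich with a normal reference, true type I error is about 7.5 to 8% with no village covariate, about 8.5% with one and about 11% with three. For random effects models with a normal reference it is about 6 to 7% (REML) or 7.5 to 10% (ML). The community-level analysis holds about 5%, but is not designated as deciding.

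These figures assume a two-sided 5% level, ICC 0.05, near-equal villages, no influential weights and unrestricted allocation. The 7.6% figure does not depend on the ICC. Higher values need more covariates, unequal village sizes or strongly unequal weights, none of which the article fixes. The article does not show that the trial's standard errors will be too small, since a correction or the community-level test may be what is used.

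**What to change.** Replace the assurance about standard errors with one designated primary test, applied separately to men and women. Any of these would serve:
- regression of village means with a t reference on 22 − p df;
- a mixed model fitted by REML with Kenward-Roger or Satterthwaite df;
- GEE with a Kauermann-Carroll corrected sandwich and t on 22 − p df. Mancl-DeRouen is not an equal substitute here, because it becomes conservative as covariates are added.

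Name the other routes as supportive. Prespecify a small set of village-level covariates, starting with the baseline village GEMS mean for the same sex, since men and women have different scales and separate models. State how the weights enter the designated analysis.

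A randomisation test over the enumerated restricted allocations is a useful optional check, since the list already exists: "A reduced list of 50 allocations from the total 466,918 restricted allocations was randomly chosen".

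The cost is analysis wording and standard software options, with no new data. Confidence intervals become slightly wider; with no covariate, the correct interval is 2.086 / 1.869 = 1.12 times the uncorrected one.

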## Discussion

This is one of the first randomized community trials of an intervention using community mobilization to address the intersection of HIV and inequitable gender norms. In the area of HIV prevention, community mobilizing interventions have demonstrated successes in increasing condom use, [3, 23, 29, 30, 42, 43] improving service access and quality, [3, 44] increasing social capital or social cohesion, [3, 45] and in promoting uptake of HIV counseling and testing [46]. Though a number of successful projects have spurred interest in the application of community mobilization for HIV prevention, most interventions utilizing mobilization to date have lacked a clear theory-based, conceptual framework or have failed to identify core CM components needed to mobilize communities around HIV prevention and care, [47, 48] something that will be critical to the scale-up of interventions that utilize mobilizing approaches. Drawing from the rich literature from sociology, community empowerment, community development, and community capacity we developed a theory based framework for community mobilization onto which we mapped and monitored our intervention activities. Ensuring that our intervention activities addressed all six theorized mobilization domains we believe increases the chances that our intervention will have an impact on the desired outcomes. In addition, as we have developed a validated, quantitative measure of community mobilization (comprised of six theorized CM domains), we will also be able to assess whether changed negative gender norms occurred through the theorized CM domains and which domains were most relevant to change.

This study has a number of strengths. First, a carefully designed and theory-driven intervention was used. Second, the intervention is being rigorously evaluated using a cluster randomized controlled trial. Third, the study is based in a demographic surveillance site which provided a sampling frame and key demographic information on the target population, including a longstanding delineation of village boundaries that is often difficult for studies to establish. Fourth, this was a true collaboration between an existing Non-Governmental Organization and Academic/Research partners allowing for the adaptation of an existing intervention, the OMC Campaign, to better align with the theory of CM and ensure rigorous monitoring and evaluation. Finally, intervention targets were set for intervention dose and reach and monitored using monthly and quarterly reports which helped ensure that the target population was reached with the intervention activities theorized to be most salient to changing gender norms.

The study also has limitations. First, the study area is characterized by high levels of in- and out-migration, mainly for work purposes. It is estimated that 33 % of men and 19 % of women in the study area are temporary migrants [33]. As a result, eligibility for survey participation included residency in the study community for the past 12 months to ensure sufficient intervention exposure at the endline survey (at which time the same eligibility criteria applied). While migrant men were not excluded from participating in intervention activities, as they are a key population to reach, they were not included in the surveys and thus we cannot make inferences about the acceptability or impact of the intervention among migrants. Second, as with all community randomized trials, there is the potential for contamination. Significant changes to Sonke’s OMC intervention model were made to reduce contamination, including elimination of mass media engagement, which is typically a central strategy in Sonke’s work. This aspect of the OMC adaptation may weaken the effect of the intervention. Other strategies to reduce contamination included ensuring that mobilizers were living in one of the intervention communities, and for some events such as soccer tournaments, being careful about where activities were conducted and which communities were invited. To measure the magnitude of contamination, intervention exposure was measured both in intervention and control communities during the endline survey.

## Conclusion

This is one of the first randomized controlled trials to test a theory-based model of community mobilization to change gender norms and prevent HIV. Determining whether this CM intervention is effective in changing harmful norms and reducing high levels of HIV risk behaviors particularly among men in this population is a matter of considerable importance for South Africa. The intervention is based on an adaptation of a widely used intervention (the One Man Can campaign) supported by substantial on-the-ground knowledge of an established, local NGO, infrastructure that could enable scale-up and sustainability in South Africa if the intervention is found to be effective.
